## Abstract

This report presents a research study plan on human subjects – the influence of stress and alcohol in simulated traffic situations under an H2020 project named
SIMUSAFE. This research study focuses on road-users’, i.e., car drivers, motorcyclists, bicyclists and pedestrians, behaviour in relation to retrospective studies, where interaction between the users are considered. Here, the study includes sample size, inclusion/exclusion criteria, detailed study plan, protocols, potential test scenarios and all related ethical issues. The study plan has been included in a national ethics application and received approval for implementation.

## Introduction

### Project overview

The
SIMUSAFE project (an acronym for “SIMUlator of behavioural aspects for SAFEr transport”) aims to analyse and define the individual variable related to risky uptake behaviour in urban traffic situations, trace cause-consequence data to evaluate risk awareness and perception and determine core factors of risky behaviour and affected decision-making processes. SIMUSAFE therefore makes use of state-of-the-art simulation, artificial intelligence (AI), virtual reality (VR) and data science methodologies to retrieve accurate actor and behavioural models in the urban traffic environment, so as to reproduce the same circumstances in incidents of interest, and thus to understand the underlying behaviour and motivations of the involved actors.

For the present human subject study, simulators have been prepared for the following scenarios and road-users:

Car driversMotorcyclistsBicyclistsPedestrians

In
Figure 1–
Figure 4, pictures (taken by ITCL) of the car, motorcycle, bicycle and pedestrian simulators are shown. The vehicle simulators include big screens and pedestrian simulators include VR goggles that simulate the specific conditions of each category.

**Figure 1. f1:**
[figure not shown]
Car Simulator.

**Figure 2. f2:**
[figure not shown]
Motorcycle Simulator.

**Figure 3. f3:**
[figure not shown]
Bicycle Simulator.

**Figure 4. f4:**
[figure not shown]
Pedestrian Simulator.

### Background

This phase of the SIMUSAFE project is focused on a major issue, stress, which affects a road user’s behaviour while actively participating in regular traffic. The growing complexity of the car and traffic environment, including the operation of assistance and information systems, can induce stress and increases cognitive load, which may affect driving performance
^
1
^. Mathews & Desmond outlined two major causes of driver stress: overload of attention and disruption of control
^
2
^. Driving environment can relate to both aspects. For example, road condition, such as road that causes excessive vibration to the vehicle, can overload driver attention and overall workload of the driver increases. This phenomenon can produce increased stress for drivers. Moreover, the environment of the road equally affects a pedestrian’s stress level while using the road. Selzer & Vinokur outlined driver stress as the prime safety problem for road users since it provides insights on driver behaviour by defining cognitive load
^
3
^. Several studies were conducted to determine the effects of stress on driving performances
^
4,
5
^. Most of these studies found that driver stress impairs driving performance and increases risk-taking behaviour to cope with stress. Risky behaviours further stimulate aggressiveness in driving performance and end up in severe crashes that harm other normal road users
^
6,
7
^.

The influence of alcohol intoxication on human behaviour in relation to traffic safety has been extensively studied over several decades. This research has been strongly motivated by the fact that a small fraction of drunk drivers, less than 1% in most countries, typically cause 25–30% of road accident fatalities
^
8
^. Legal limits for breath and blood alcohol concentration have been established in most countries based on physiological research establishing the blood/breath transition, which Jones and Hlastala showed in their studies
^
9,
10
^. In an extensive retrospective case-study by Blomberg
*et al.*
^
11
^, it was established that the accident risk increases rapidly and progressively with alcohol concentration. The results are summarized in
Table 1, showing that below the Swedish breath alcohol concentration (BrAC) legal limit of 0.1 mg/L, the risk increase is only a few percent. In the interval of moderate intoxication close to the legal limit in most EU countries (0.2–0.3 mg/L), the risk increase is considerable, 18–69%, whereas in the interval 0.4–0.6 mg/L of high intoxication, the risk increase is several hundred percent.

**Table 1. T1:** Influence of breath alcohol concentration (BrAC, mg/L) on relative accident risk, based on the publication
^
11
^.

Category	BrAC Interval (mg/L)	Relative Accident Risk Interval
Sober	0-0.1	1.00-1.03
Moderately intoxicated	0.2-0.3	1.18-1.69
Highly intoxicated	0.4-0.6	2.69-8.90

In recent years the technology for contactless breath alcohol analysis has evolved
^
12,
13
^, raising the feasibility and awareness of new solutions for passive in-vehicle detection
^
14,
15
^.

Simulators for vehicle driving have been known for decades, but to our knowledge no studies have been performed so far to investigate the influence of stress and alcohol intake on driver performance in a simulated environment, and to compare these results with other study results.

The potential benefits of advanced simulators should be obvious both in research and for educational purposes. The possibility to assess and improve behaviour could potentially improve traffic safety, saving lives and preventing injuries and damage related to traffic accidents. The main motivation of such studies is it cannot be conducted in realistic conditions, and as such, the simulator provides a faithful alternative, from which many behaviors could be inferred and again this can provide the possibility of the observation of simulator bias.

### Study objective

The main study objective is to evaluate the performance of drivers’ in simulators with respect to the influence of stress and alcohol consumption on road-user behaviour in relation to our knowledge no studies have been performed.

This study is motivated by the following research questions:

i. How do different road conditions and situations impact the driver’s behaviour? Is the driver’s behaviour different with respect to the same conditions/situations if the driver is experiencing stress? Does the physiological stress change the risk potential of specific situations?ii. Alcohol related question: Is there any correspondence between the behavioural results of the study and the dependency of accident risk on alcohol concentration according to retrospective studies, e. g. Blomberg
*et al.*
^
11
^?iii. Are there any unexpected results from the study?

## Protocol

### Selection of participants

A total number of 90 participants will be recruited for the study on the overlap between stress and alcohol. The Sweden population in 2019 (National Institute of Statistics of Sweden) is approximately 10 million, the population between 18 and 65 years old is less than 5 million
^
1
^. In order to have a significant sample and using one of the most common calculus
^
2
^ to calculate samples with 5M of population, error of 10% and a confidence level of 95 % the sample size must be at least 45 users. Here in this study, two age groups are selected as a result a portion of the population is dropped. The sample size for the test will be 100 users and a 10% more taking into account possible drop offs. However, for stress and alcohol test we are going have 45 subject each as
3 and
4 consider 20 to 30 subjects for statistical significance.

The selection will be made from a larger number of people who will be asked to fill out a questionnaire, and who will also be interviewed to establish their qualifications to be enrolled as participants. The related information sheet, consent form and questionnaire are provided as
*Extended data*
^
16
^.

Each recruited participant will be called to the test site on two occasions, once for stress-related tests and once for alcohol-related tests. The test subjects are divided into two age groups: young (18 – 25 years) and elderly (50 – 70 years) as these age groups have variation in the performance according to the recent research. Sametime, it was also observed that the age between 25 and 49 are often stable in their driving performance. Participants for the stress test will receive a gift card of worth 1500 SEK as gratification for successfully completing all stages of the test. For alcohol test participants the amount of gratification is 2000 SEK.
Table 2 and
Table 3 demonstrate the approximate number of participants from different age groups and road user types, respectively.

**Table 2. T2:** Number of subjects from different age groups.

Tests	Young adult	Elderly	Total
*Alcohol*	20	25	45
*Stress*	20	25	45
**Total**	40	50	90

**Table 3. T3:** Number of participants from different road user types.

Actors	Young adult	Elderly	Total
*Car drivers*	5	7	12
*Motorcyclists*	5	6	11
*Cyclists*	5	6	11
*Pedestrians*	5	6	11
**Total**	20	25	45

Being the first investigation of its kind, this study is exploratory rather than confirmatory (i.e., a hypothesis test). Therefore, it is not meaningful to perform a statistical power analysis. The size of the study population has been established from the estimated division into age groups and other category divisions with the purpose of obtaining exploratory quantitative results.

Inclusion criteria for the participants are:

Age: young adults (18 – 24 years) and elderly (50 – 70 years)Gender: male or femaleDriving license: yes (for car drivers and motorcyclists) Health/medicine: none (i.e., participant shouldn’t have any health related problem e.g. diseases and not be taking any medication)Language: English or SwedishBody height: 160 – 210 cmBody weight: 60 – 150 kgAlcohol usage: 5 –15 glasses per month (applicable for alcohol test only)Stress tolerance: only subjects with standard or high scores in the Vienna test measuring stress tolerance and flexibility.

Exclusion criteria for participant selection are motion sickness, problems using VR goggles, stress intolerance, hearing or vision impairment, presence of chronic disease or serious allergies and any relation such as teacher and student or employer and employee among the participants and researchers. Habitual computer games players will be excluded if they are expected to be “immune” to simulated stressful situations.

Based on the study plan a press release named ‘
Smarter AI vehicles with the help of citizens in Västerås’ has been posted on the Mälardalen University website. In the press release there is a Google form link that the participants can fill in and an email address for direct contact if they wish to participate in the study.

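### The survey formula with the stated inputs gives 97, not 45, and the section leaves 45, 100 plus 10% and 90 unreconciled

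*Protocol article*

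**What the plan says.** All of this stands in the protocol article under Selection of participants, unless noted.

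- The section opens with 90 participants to be recruited.
- It then derives a minimum by "using one of the most common calculus" for a population of 5 million: "error of 10% and a confidence level of 95 % the sample size must be at least 45 users". The formula's source is a footnote that is not shown, and no expected proportion is given.
- Next comes a different figure: "The sample size for the test will be 100 users and a 10% more taking into account possible drop offs".
- The following sentence, which opens with a contrast, sets 45 subjects for each test because two sources "consider 20 to 30 subjects for statistical significance".
- Each recruited participant is to come twice, once for each test. Table 2 shows 45 for alcohol and 45 for stress and adds them to 90. Table 3 splits 45 into 12 car drivers and 11 each of motorcyclists, cyclists and pedestrians. Table 8 (Schedule) plans each main study with 45 participants.
- Later the section calls the study exploratory, says "it is not meaningful to perform a statistical power analysis", and attributes the size to the division into age groups and other categories.

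**The concern.** The formula is the only numerical derivation of sample size in the article, and its result does not follow from its inputs. A reader who trusts it will believe that 45 people give a 10% error at 95% confidence.

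The recruitment target is also unclear. Three figures stand side by side, a drop-out allowance is announced but does not appear in the tables, and the unit being counted is uncertain. Someone checking later whether the study reached its planned size would not know which number to use.

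**Working it through.** **Inputs.** From the section: N = 5,000,000, error e = 0.10, confidence 95% (two-sided z = 1.96). Assumed: p = 0.5, the customary worst case when no proportion is given.

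**The plan's own figure.**

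- n0 = z² p(1 − p) / e² = 1.96² × 0.25 / 0.01 = 96.04
- Finite-population correction: n0 / (1 + (n0 − 1)/N) = 96.03, so 97

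The stated 45 is not reproduced. Dropping part of the population because only two age groups are studied does not help: with N = 1,000,000 the result is still 96.03.

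**Standard variants at 10% and 95%.**

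| Variant | n |
|---|---|
| Two-sided z, p = 0.5 | 97 |
| One-sided z, p = 0.5 | 68 |
| z rounded to 2 | 100 |
| Yamane, N/(1 + N e²) | 100 |

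**What would give 45**, changing one input at a time:

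- p: p(1 − p) = 45 × 0.01 / 1.96² = 0.117, so p is about 0.136
- error: 1.96 × √(0.25/45) = 0.146, so 14.6 points
- confidence: 2Φ(0.10 × √(45/0.25)) − 1 = 2Φ(1.342) − 1 = 0.82
- population: about 84 people

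The result is sensitive to p (35 at p = 0.10, 62 at p = 0.20, 81 at p = 0.30), but nothing in the article supports a p near 0.14. The next figure in the section, 100, does fit the formula. With 90 people the margin is 1.96 × √(0.25/90) = 10.3 points.

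**The recruitment figures.**

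- 100 × 1.10 = 110.
- Table 2: 45 + 45 = 90, and Table 8 schedules exactly 45 per test. No 10% is added to either. If 45 are recruited and 10% are lost, about 40 complete.
- If 90 different people each attended both tests, each test would have 90, not 45. If 45 people attend both, 90 counts attendances. If 90 people are split 45 and 45, the statement that each comes for both tests is wrong.

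**Precision that 45 gives for the comparison planned.** The stress test is a within-participant design, and the alcohol test compares each subject sober and after drinking. For a mean within-person difference, the 95% half-width in units of the SD of that difference is t(0.975, n − 1)/√n:

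| n | Calculation | Half-width |
|---|---|---|
| 45 (pooled) | 2.015/√45 | 0.30 SD |
| 40 (after 10% loss) | 2.023/√40 | 0.32 SD |
| 12 (one road-user type) | 2.201/√12 | 0.64 SD |
| 11 (one road-user type) | 2.228/√11 | 0.67 SD |

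**The case against.** The strongest reply is that the formula does not carry the design. The section gives two other grounds for 45 per test: the 20 to 30 subjects in cited sources, and the category divisions of an exploratory study. No objective or analysis in the article estimates a population proportion, so the 10% margin is not a result the study would report. This stands, and it limits the consequence. It does not make the printed 45 correct, and the exploratory paragraph does not withdraw it.

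Four stronger conclusions are tempting but are not supported:

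- *The study is too small and needs 97 people.* The formula answers a question the study does not ask, so its correct result is not a target for this design.
- *Declining a power analysis contradicts the formula.* A precision formula and a power analysis are different calculations. The fair point is that one number is given two unrelated bases.
- *The 20 to 30 criterion fails because each road-user type has only 11 or 12.* The sources are not shown, so the criterion may apply per test, where 45 exceeds it. For alcohol, the test at the high level is described as performed in all simulators, so 11 or 12 per type may not apply there.
- *Recruitment is 20 short of 110.* The contrasting sentence can be read as replacing the 100, and 90 may count attendances. The figures are unreconciled, but a shortfall is not established.

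**Conclusion.** The point holds in two parts.

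First, 45 does not follow from the stated inputs: the result is 97 at p = 0.5, and no standard variant at 10% and 95% gives 45. This rests on the default p, since the article states none and the formula's source is not shown. At 45 the margin for a proportion is 14.6 points, not 10.

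Second, and without any assumption, the section leaves 45, 100 plus 10%, and 90 unreconciled, shows no drop-out allowance in its tables, and does not make clear whether 90 means people or attendances.

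This is an error in the stated justification. It does not show that the exploratory design is unsound.

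**What to change.** - Delete the survey-formula derivation, together with the claim of a significant sample and the sentence on 20 to 30 subjects. Replacing 45 with 97 would not do: the text presents the figure as a minimum, and neither 45 nor 90 would meet it.
- State one recruitment figure, say whether it counts people or test attendances, and say how drop-outs are handled. Bring Tables 2, 3 and 8 and the sentence on two occasions into line with it.
- Keep the exploratory basis and add the precision achieved: a 95% half-width of about 0.30 SD of the within-person difference for 45 pooled (0.32 SD if about 40 complete), and about 0.64 to 0.67 SD wherever results are reported for one road-user type of 11 or 12.

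The cost is wording only, with no extra participants. The one downside is that the stated precision becomes less favourable than the text now implies.

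### The stated minimum of 45 users does not follow from the inputs given for it: the usual survey formula gives 97, and the same paragraph also says 100 plus 10%

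*Protocol article*

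**What the plan says.** Under Selection of participants, the protocol article gives several accounts of its sample size.

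- **Survey calculation.** The method is described only in general terms: "In order to have a significant sample and using one of the most common calculus". It takes a population of 5 million and states the other inputs and the result together: "error of 10% and a confidence level of 95 % the sample size must be at least 45 users". The 5 million refers to Swedish residents aged 18 to 65: "the population between 18 and 65 years old is less than 5 million".
- **A larger figure in the same paragraph.** "The sample size for the test will be 100 users and a 10% more taking into account possible drop offs".
- **The planned numbers.** The paragraph then sets 45 for the stress test and 45 for the alcohol test, citing sources that work with 20 to 30 subjects. Table 2 shows 45 per test and 90 in total. Table 3 divides 45 into road-user types of 12, 11, 11 and 11.
- **Exploratory status.** The text after Table 3 calls the study exploratory and says of power: "Therefore, it is not meaningful to perform a statistical power analysis". It attributes the size to the division into age groups and other categories.
- **Attendance.** The section also says that every recruited participant comes twice, once for each test. Table 9 under Ethical issues agrees, putting the effort for a test subject at two working days.

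**The concern.** The inputs and the result are both printed, so the step can be checked, and it does not reproduce. The stated minimum also equals the number planned for each test. A reader who sees 45 required and 45 planned may conclude that each test achieves ±10 points at 95% confidence, which it does not under the usual assumption. The following sentence, with 100 users plus 10%, cannot be squared with either 45 or 90, so the paragraph leaves the intended sample size unclear.

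There is also a mismatch of method. The survey formula gives the margin for one proportion in a random sample of a population. The Design and procedure section describes a within-participant stress test and an alcohol test that compares each person sober and after drinking, in screened volunteers.

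**Working it through.** **Inputs from Selection of participants:** N = 5,000,000; error e = 0.10; 95% confidence, z = 1.96 (two-sided); stated result 45. **Assumed:** p = 0.5, because no expected proportion is given.

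**1. Attempt to reproduce 45.**
- n0 = z²p(1−p)/e² = 1.96² × 0.25 / 0.10² = 96.04.
- With the finite-population correction, n = n0 / (1 + (n0 − 1)/N) = 96.04 / (1 + 95.04/5,000,000) = 96.04, rounded up to **97**.
- The stated 45 is not reproduced.

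**2. Other common versions, with the same N and e and p = 0.5 where it enters.**
- One-sided 95%, or 90% confidence (z = 1.645): 67.6, so 68.
- z = 2, or the shortcut N/(1 + Ne²): 100.

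**3. Sensitivity to the unstated proportion (95%, e = 0.10).**

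| p | n |
|---|---|
| 0.1 | 35 |
| 0.135 | 45 |
| 0.2 | 62 |
| 0.3 | 81 |
| 0.4 | 93 |
| 0.5 | 97 |

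**4. What would have to change to give 45, one input at a time.**
- Proportion: about 0.135 (or 0.865).
- Confidence: z = 0.10 / (0.5/√45) = 1.342, which is about 82%.
- Error: 1.96 × 0.5/√45 = 0.146.
- Population: N = 45 × (96.04 − 1)/(96.04 − 45), about 84.

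The article remarks that selecting two age groups drops part of the population. That cannot explain 45: even N = 100,000 gives 95.95. For the same reason, the difference between the 18 to 65 population and the ages actually recruited has no numerical effect.

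**5. Margin that the planned numbers give (95%, p = 0.5).**
- n = 45: 1.96 × 0.5/√45 = **±14.6 points**.
- n = 90, if these are 90 different people: 1.96 × 0.5/√90 = ±10.3 points.

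**6. The figures side by side.** The 100 users agree with the 97 to 100 found in steps 1 and 2. Adding 10% gives 110, or 112 if 100 completers are wanted after 10% loss (100/0.9 = 111.1). Neither matches 90. If 90 people each attended both tests, each test would have 90, not 45. If the same 45 attended both, the total would be 45 people, not 90.

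**7. Precision on the scale of the design.** For a mean within-person change, with a t-interval, the 95% half-width in SDs of the differences is t(0.975, n−1)/√n: 2.015/√45 = 0.30 for n = 45; 2.201/√12 = 0.64 for n = 12; 2.228/√11 = 0.67 for n = 11.

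**The case against.** **The proportion is not stated.** The article names no formula and gives no p, so 97 is not strictly its own figure, and a proportion near 0.135 would give 45. This stands as a limit on wording: 45 fails to reproduce under the usual default, but it is not impossible under every input. Nothing in the text supports 0.135, however, and the 100 users in the next sentence point to p = 0.5.

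**The 45 per test has other grounds.** The article also cites the 20 to 30 subjects used elsewhere and says that the size came from age groups and other categories. This stands. A reader might infer that the study was sized to ±10 points and misses its own standard. The document does not support that, because it attaches no ±10-point margin to any outcome and does not rest the 45 per test on the formula alone.

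**The study is exploratory.** This excuses the absence of a power calculation. It does not make a printed calculation correct.

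**Precision for within-person changes belongs in an analysis plan.** This is fair. The Data/statistical analysis section names data mining, fuzzy modelling and machine learning, and no estimate of a mean change, so the half-widths in SD units are an optional addition and not a correction.

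**Conclusion.** The stated minimum of 45 is wrong as written. Under p = 0.5 the stated inputs give 97, more than twice as many, and 45 people give ±14.6 points. The conclusion rests on reading the 10% as an absolute margin, on 95% two-sided confidence and on p = 0.5. A proportion of 0.2 or 0.3 would still require 62 or 81. Apart from p, the contradiction between a minimum of 45, a planned 90 and 100 plus 10% stands on the article's own text.

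A reader might go further and infer that the study is too small or should recruit 97. That does not follow. The formula is not suited to within-participant changes, so 97 would correct the arithmetic without showing that any sample is adequate. The fault lies in the stated justification. It should be fixed, but no power claim depends on it.

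**What to change.** 1. Delete the formula-based minimum of 45. Alternatively, correct it to 97, state that p = 0.5 is assumed, and say that 45 per test gives ±14.6 points.
2. Rest the 45 per test on the grounds that the article otherwise gives: the division into age groups and road-user types, and the exploratory aim.
3. Reconcile 45 per test, 90 in total and 100 plus 10%. Say whether 90 different people are meant, given that each participant is said to attend both tests.
4. Optionally, add the precision for a within-person mean change: a 95% half-width of about 0.30 SD of the differences for n = 45, and 0.64 to 0.67 SD for a single road-user type (n = 12 or 11).

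The cost is one reworded paragraph, with a less favourable precision if a margin is kept. No extra participants are needed.

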A number of different physiological data will be collected; heart rate (HR), heart rate variability (HRV), blood volume pulse (BVP), electromyogram (EMG), galvanic skin response (GSR), EEG and electro-oculogram (EOG). For the alcohol test, one additional measurement on BrAC will also be measured. These data will be used to produce model that can give objective measurements of stress and alcohol presence, and as a basis for assessing risky behaviours of road users by corelating with data from the Vienna test and simulators.

**
*Schedule*.** The tentative time plan for each of the steps for experiments on effects of stress and alcohol on road users are outlined below in
Table 8.

**Table 8. T8:** Schedule of various parts of the experiment.

Date	Events
2020-06-01 –	Advertisement for volunteers for stress and alcohol tests
2020-09-16 – 2020-10-31	Information meeting, questionnaire and feedback session for stress and alcohol tests
2020-09-20 – 2020-11-15	Selection of volunteers and signing of consent forms for stress and alcohol tests
2020-10-16 – 2020-11-30	Cognitive assessment by Vienna test of volunteers for stress test
2020-12-01 – 2021-01-15	Cognitive assessment by Vienna test of volunteers for alcohol test
2021-01-15 – 2021-01-31	Pilot study for stress test
2021-02-01 – 2021-02-15	Pilot study for alcohol test
2021-02-16 – 2021-03-31	Main study for stress test with 45 participants
2021-02-20 – 2021-04-05	Self-confrontation interviews for stress test
2021-04-01 – 2021-05-31	Main study for alcohol test with 45 participants
2021-04-16 – 2021-05-15	Self-confrontation interviews for alcohol test
2021-04-16 – 2020-05-20	Miscellaneous tasks

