### Study status

The status of the study is now on hold due to Covid-19 restriction since November 2020. However, there was interest from 127 participants in total and 50 were invited for the information meeting, with 43 having performed the cognitive tests before November 2020.

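### The plan states both 90 recruits and 100 users plus 10% for drop-offs, and applies the drop-off allowance to no planned number

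*Protocol article*

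**What the plan says.** All the sizing statements but one stand in the Selection of participants section of the protocol article.

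- Total to recruit: "A total number of 90 participants will be recruited for the study on the overlap between stress and alcohol".
- Derived minimum, for a population of 5 million: "error of 10% and a confidence level of 95 % the sample size must be at least 45 users".
- Larger total with an allowance: "The sample size for the test will be 100 users and a 10% more taking into account possible drop offs".
- Number per test, in the very next sentence: "However, for stress and alcohol test we are going have 45 subject each as". The reason given is that cited sources regard 20 to 30 subjects as enough.
- Table 2: 45 for alcohol and 45 for stress, summed to 90. Table 3: 12 + 11 + 11 + 11 = 45 by road-user type. The text calls both tables approximate.
- After Table 3, the section says that the study is exploratory, that a power analysis would not be meaningful, and that the size comes from the division into age groups and other categories.

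The remaining statement is in Table 8, under Schedule: "Main study for stress test with 45 participants" and "Main study for alcohol test with 45 participants".

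The figures 100 and 110 are used nowhere else, and no other place adds a drop-off allowance to 90 or to 45.

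**The concern.** A sample size and a drop-off allowance are stated in the future tense, as what will be done, and the design contains neither. Someone using the article to plan recruitment cannot tell whether to stop at 90, 100 or 110. Someone reading it to judge the results would believe that a 10% reserve exists.

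The status of the 45 is also unclear. The tables do not say whether it is the number before or after drop-off. With no reserve, any loss comes straight off the 45.

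**Working it through.** **1. The plan's own derived figure.** The stated inputs are a margin of error e = 0.10, 95% confidence (z = 1.96) and N = 5,000,000. The plan gives no proportion, so p = 0.5 is an assumption here (the usual conservative choice).

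- n = z² p(1 − p) / e² = 3.8415 × 0.25 / 0.01 = 96.04, so 97.
- With the finite-population correction, n / (1 + (n − 1)/N) = 96.03, still 97.
- The stated minimum of 45 is not reproduced. Two-sided 90% (or one-sided 95%) gives 67.6, so 68; two-sided 80% gives 41.1, so 42. At 95% confidence, 45 would need p of about 0.136.
- Margin at a given n is 1.96 × √(0.25/n): 14.6% at n = 45, 10.3% at n = 90 and 9.8% at n = 100.

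With p = 0.5, then, the stated inputs fit the figure of 100 and not the figure of 45.

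**2. The two totals.**

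- 100 plus 10%: 100 × 1.10 = 110. If the allowance is read as dividing by the retained share, 100 / 0.90 = 111.1, so 112.
- Planned recruitment: 45 + 45 = 90.
- Gap: 110 − 90 = 20 (20/110 = 18%), or 22 against 112. Against the uninflated 100 the gap is 10.

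**3. Does another reading close the gap?**

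- *100 is 90 already inflated.* 90 / 0.90 = 100 exactly, but the text adds 10% on top of 100 and says that 90 will be recruited.
- *Persons or person-tests.* The section says that each participant attends twice, once per test, yet Table 2 sums 45 and 45 to 90. So 90 may mean 90 persons, or 45 persons tested twice. Neither gives 100 or 110.

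**4. Size of the effect on each test.** The plan attaches the 10% to the 100, so using it for the 45 is conditional.

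- 45 × 0.90 = 40.5, about 40 per test.
- Keeping 45 after a 10% loss would take 45 / 0.90 = 50 enrolled.
- The 95% half-width for a mean within-person change, in SDs of the change, is t / √n. It is 0.30 at n = 45 and 0.32 at n = 40.

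**The case against.** The strongest reply is that the plan answers the point itself. Straight after the larger total it turns to the two tests, sets 45 for each and gives a reason. On that reading 100 plus 10% is a general figure from which the plan knowingly departs. This stands as an explanation of 45 per test. It does not explain why the larger total is still stated as what will happen, and it does not carry the allowance over to 45 or 90.

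A second reply is that participants are chosen from a larger pool, with 127 people interested according to Study status, so losses could be made good. That limits the practical harm, but the pool is described for screening and no replacement rule is tied to it.

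A third is that the study is exploratory. That is right, and it is why the consequence is modest. It excuses the absence of a power calculation, not two incompatible totals.

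Some stronger readings are tempting but unsupported:

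- A reader might infer that the tables promise completers, or pass off an enrolment count as an analysis count. They count subjects or participants, Tables 2 and 3 only approximately, and no expected number of completers is given anywhere.
- A reader might infer that the smallest age-by-road-user cells will bear the loss. Nothing in the article says where drop-offs would fall.
- A reader might take the Study status line, "50 were invited for the information meeting, with 43 having performed the cognitive tests before November 2020", as an observed drop-out rate. It describes recruitment interrupted by the Covid-19 hold. In Table 8 the information meetings start before selection and consent, and the cognitive (Vienna) test is itself part of eligibility. It is not loss after enrolment.

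**Conclusion.** The point holds as an internal contradiction. One paragraph gives 90 recruited and 100 plus 10%, and the stated drop-off allowance reaches no planned number. The gap is 20 people (18% of 110), or 10 against the uninflated 100. This rests on the stated figures alone and needs no assumption beyond reading the allowance as 100 × 1.10; the other common reading, 112, widens the gap.

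The practical consequence is modest. About 40 per test instead of 45 is conditional on a 10% loss in each test, and it would widen the interval for a within-person change from 0.30 to 0.32 SD. No power claim is broken, because none is made.

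The derivation of at least 45 cannot serve as the surviving basis for the size. With p = 0.5 assumed, its inputs give 97, and 45 gives a margin of about 14.6%.

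**What to change.** In Selection of participants:

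1. State one total, and say whether 90 counts persons or person-tests.
2. Replace the sentence giving 100 users plus 10% with something like: 45 participants are enrolled per test; no drop-off reserve is included; if 10% were lost in each test, about 40 would complete.
3. Stop presenting at least 45 as the result of 10% error and 95% confidence. Either remove that calculation, or report it correctly with its assumed proportion (97 at p = 0.5; margin about 14.6% at 45). Rest the size on the basis already given after Table 3, the division into age groups and other categories.
4. Label the numbers in Tables 2, 3 and 8 as enrolled.

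The cost is wording in one paragraph and three table labels. The stated size becomes less favourable, since the larger total and the reserve disappear. If the sponsor does want to end with 45 per test after a 10% loss, that would mean enrolling 50 per test, which is a recruitment cost and not a wording change.
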